Clinical Effectiveness and Preventive Impact of Home Zinc Treatment for Acute Diarrhea in Children: A Cluster-randomized Field Trial in Rural Western Kenya

KEMRI SSC # 985; CDC IRB # 4678

Amended August 27, 2007

Investigators.

[name], MSPH, Epidemiology Section Chief, CDC International Emerging Infections Program, Kenya.

[name], SUZY Project Principal Investigator, Director, Health Systems & Infectious Diseases Division, International Center for Diarrheal Disease Research (ICDDR,B), Bangladesh

[name], Director, CDC International Emerging Diseases Program Kenya.

[name], BSc. Nutritionist, CDC/KEMRI.

[name]. Malaria Branch Chief, CDC/KEMRI Field Station, CDC

[name]. CDC/KEMRI Field Station Director, Kisumu Kenya

[name]. Director, Division of Child Health, Kenya Ministry of Health.

[name]. Director, Centre for Vector Biology and Control Research, Kenya Medical Research Institute

[name], Director, CDC/KEMRI Field station, Kisumu, Kenya

Abstract.

Background. Zinc deficiency is common in Africa. It has been shown in Asia that zinc as treatment for diarrhea can shorten the course of episodes of diarrhea, as well as prevent future episodes. The use of zinc at home to treat diarrhea in an African setting, where malaria, HIV and malnutrition are common, has not been well-studied.

Objective. To evaluate if zinc treatment for diarrhea given at home in Kenyan children will decrease the community prevalence of diarrhea more than zinc given only in the clinic

Work planned. We propose to do a community-randomized intervention study of 10 days of dispersible zinc tablets given in the home, in addition to ORS, to treat diarrhea in children under-5 years of age living in a rural part of Bondo District. The comparison group will be children who receive zinc and ORS in the clinic only. The primary outcome will be a comparison of the prevalence of diarrhea in home zinc versus nonhome zinc villages. Secondary outcomes will be the incidence of repeat episodes of diarrhea, the duration of diarrheal illness, the prevalence of acute respiratory infection, and the effect of malaria infection on treatment with zinc. Thirty-three villages (approximately 1300 children) will be enrolled and children will be followed for 1 year.

Significance of results. If this study shows zinc given at home to be effective, this might be considered by the Kenyan MOH as an essential component of the treatment of diarrhea in children at the community level.

Background.

Zinc deficiency has been found to be widespread among children in developing countries, and occurs in most of Latin America, Africa, the Middle East and South Asia (Shrimpton R 1993). Clinical and field studies have consistently observed an association between zinc deficiency and infectious disease morbidity (Srinivas U et al. 1988, Bahl R et al. 1998). Zinc deficiency is associated with a higher rates of infectious diseases, including skin infections, diarrhea, respiratory infections, malaria, and delayed wound healing (Aggett PJ & Comerford 1995, Prasad AS 1985, Bahl R et al. 1998). The higher rate of infectious diseases in zinc deficient children, however, is often multifactorial as they are often also malnourished and might have a preponderance of other risk factors for infection. Despite this caveat, some have estimated that based upon the impact of zinc deficiency on diarrheal disease, it is estimated zinc could prevent nearly 500,000 diarrhea related under-five deaths annually (Black RE et al. 2003, Jones et al. 2003).

Several recent randomized controlled trials have demonstrated the beneficial role of zinc in the prevention and treatment of diarrhea and pneumonia (Sazawal S et al. 1995 and 1998, Zinc Investigators Collaborative Group 1999, Zinc Investigators Collaborative Group 2000, Shanker AJ 2000, Fontaine O 2001, Bhutta ZA et al 2001, Baqui AH et al 2002, Strand TA et al. 2002, Bhandari H et al. 2002). Meta-analyses of published zinc treatment trials estimate that children between 3 months and 5 years of age who receive zinc for the treatment of a diarrheal illness (20 mg/day for 10 days) recover faster, with a 25% reduction in duration of illness and a 35% reduction in the severity of the illness. Furthermore, there is about a 30% reduction in the likelihood of developing prolonged diarrhea. Moreover, it has been shown that there is a beneficial effect of zinc treatment for children with and without zinc deficiency, although the effect is slightly greater in those with zinc deficiency (Zinc Investigators Collaborative Group 2000). These are the clinical treatment benefits. There are also longer-term beneficial effects. Over the 3 to 6 months following supplementation initiation, there is an estimated 30% decreased likelihood of a subsequent episode and 50% reduction in non-injury mortality (Zinc Investigators Collaborative Group 1999, Zinc Investigators Collaborative Group 2000, Fontaine O 2001, Bhutta ZA et al 2001, Baqui AH et al 2002, Strand TA et al. 2002). There are also preventive effects from use of zinc for treatment of diarrhea. In one community-randomized cluster study in Bangladesh, children in villages that received a 14 day course of zinc for diarrhea (completed 7 days on average), there was a 24% decrease in the duration of the diarrhea episode and a significant 15% decrease in diarrhea incidence over the study period (Bacqui AH et al 2002). There was also a 7% decrease in the incidence acute respiratory infections in the zinc villages compared with the control villages during the study period. Based on these data WHO and UNICEF came out with joint guidelines in 2004 for the inclusion of zinc in the treatment of acute diarrhea episodes for children under 5 years of age. (WHO/UNICEF Joint Statement 2004).

Why does zinc have a therapeutic and preventive impact on diarrheal illnesses? The available evidence of zinc’s potential role is derived from randomized clinical trials of zinc treatment or supplementation, that were not designed to explain why zinc is as effective as it seems to be. Zinc has been identified to play critical roles in function of metallo-enzymes, poly-ribosomes, cell membrane, and other cellular components, leading to the understanding that it also plays a central role in cellular growth and in function of the immune system (Shankar AH et al. 1998, Ibs K-H et al. 2003). With moderate zinc deficiency, epithelial barriers are compromised and multiple components of the immune system malfunction.

Although the zinc plasma pool is small, a concentration of 12-16 umol/L is extremely important for immune function in normally nourished children, it. Zinc deficiency in children is known to adversely affect innate and active immunity. Natural killer cell function, as well as phagocytosis by macrophages and neutrophils, are impaired by even mild zinc deficiency (Hasegawa W et al. 2000, Ravaglia G et al. 2000, Hock H et al. 2003, Shibuya A 2003). Also affected is the proliferation and function of cytotoxic T cells (Shankar AH et al. 1998). The obvious conclusion is that zinc deficiency results in diminished immunological competence, that in turn leads to an increased risk for infectious diseases and greater severity of illnesses.

At the urging of WHO and with their financial support, a French firm specializing in nutrition products for humanitarian aid (Nutriset, Ltd) and a French pharmaceutical laboratory (Rodael) developed a dispersible zinc tablet formulation. The zinc is encapsulated in a vanilla flavored coating that effectively masks the taste of zinc. Acceptability studies in Bangladesh, Tanzania, and elsewhereuniformly find the product is well received by young children (Nasrin D et al, in press). The dispersible tablets are packaged in a PVC/Alu blister pack of 10 tablets at an approximate cost of 14 cents US/blister pack. The current shelf life is 3 years and is expected to rise. It is stable in climates with high humidity and temperatures.

Although zinc use for the treatment of diarrhea has been well-studied in Asia, few studies of its use have been done in subSaharan Africa (Table 1). All three studies that evaluated the impact on diarrhea showed a decrease in diarrhea, although in one study this beneficial effect was only observed in growth-stunted children (Umeta M, 2002, Muller O, 2001, Makonnen B, 2003). However, in all of these studies zinc was given for prevention only, not for treatment. Two of these 3 studies also showed a decrease in ARI and fever. Two additional studies among African children evaluated malaria as the primary outcome – one from the Gambia showed a 32% decline in clinical malaria with zinc prophylaxis; however, a large multi-center study showed no change in parasitologically confirmed malaria . A large study of zinc supplementation for children in Pemba, Tanzania was recently published, showing a nonsignificant decrease in mortality among children who got zinc supplementation, although there was a significant decrease in those one year of age and older. (Sazawal S, et al 2007).

Table 1. Summary of studies of zinc on morbidity in Africa. Several more studies on growth parameters not included.

| Syndrome/site | How zinc given | Design | participants | 1o outcome measured | How 2o outcome defined | Results | Ref |
| --- | --- | --- | --- | --- | --- | --- | --- |
| Diarrhea |  |  |  |  |  |  |  |
| Ethiopia | 6 days/wk x 6 months | RCT, 50 zn, 50 placebo in both stunted and nonstunted | Stunted and nonstunted infants | Growth | History >3 loose stools/24 hrs | Significant decrease in stunted, not nonstunted | Umeta M, 2000 |
| Burkina Faso | 6 days/wk x 6 months | RCT, 709 enrolled | Children from a DSS | Malaria | “diarrhea” | Relative risk 0.87 (95% CI .79-.95) | Muller O, 2001. |
| Lesotho | 90 days daily after admission | RCT, 150 zn, 150 placebo | Children admitted with malnutrition | Multiple | History of diarrhea | Decreased in zn group at 30, 60, 90 days | Makonnen 2003 |
| ARI |  |  |  |  |  |  |  |
| Ethiopia | 6 days/wk x 6 months | RCT | Stunted and nonstunted | Growth | Cough | Significant decrease in stunted, not nonstunted | Umeta, 2000 |
| Burkina Faso | 6 days/wk x 6 months | RCT | From DSS | Malaria | Cough | No Difference | Muller, 2001. |
| Lesotho | 90 days daily after admission | RCT | Children admitted with malnutrition | Multiple | ? | Decreased in zn group at 30, 60, 90 days | Makonnen,, 2003 |
| Fever |  |  |  |  |  |  |  |
| Ethiopia | 6 days/wk x 6 months | RCT | Stunted and nonstunted | Growth | fever | Significant decrease in stunted, not nonstunted | Umeta, lancet 2000 |
| Burkina Faso | 6 days/wk x 6 months | RCT | From DSS | Malaria | fever | No Difference | Muller, 2001. |
| Lesotho | 90 days daily after admission | RCT | Children admitted with malnutrition | Multiple | fever | Decreased in zn group at 30, 60, 90 days | Makonnen, 2003 |
| Malaria |  |  |  |  |  |  |  |
| Burkina Faso | 6 days/wk x 6 months | RCT | From DSS | Malaria | Various ways | No Difference in incidence or severity | Muller O, 2001. |
| Uganda, Ghana, Tanz, Zambia, Ecuador | Supplement to treatment x 4 days | RCT, n = 1087 | Clinics | Malaria | fever, parasitemia, Hb | No difference | Zinc against Plasmodium group 2002. |
| Gambia | Twice weekly | ?, N=110 | Clinics | Malaria | clinical malaria | 32% reduction | Bates 1993. |

Other treatments, such as antimalarials, have been employed successfully using home-based treatment in Africa (Dunyo SK et al). There have been no studies of home zinc treatment for diarrhea in Africa. However, in Mali a program of community based zinc treatment of diarrhea by community health workers showed high acceptance and compliance by mothers (Ellis AA et al, 2006. Winch PJ et al, 2006). The major problem identified in the Mali project was that often mothers opted to give their children zinc alone when they had diarrhea accompanied by other symptoms, such as fever and cough, which required antimicrobial agents. (personal communication [name] from the nonpublished manuscripted entitled “Lessons learned in a pilot introduction of zinc treatment for childhood diarrhea in Bougoni District, Mali”). This problem was addressed and rectified by re-education of community workers and mothers. This point will need to be emphasized and monitored closely in any program of home-based zinc treatment of diarrhea.

Important questions remain regarding the use of zinc in subSaharan Africa.

1. Will zinc used as an adjuvant treatment for diarrhea have the beneficial effects seen in Asian studies? The spectrum of pathogens causing diarrhea are different in many African settings. Whereas enterotoxigenic *E. coli* and cholera are common in south Asia, these pathogens are relatively rare as causes of nonepidemic diarrhea in Africa, where *Shigella*, *Salmonella*, *Campylobacter* and rotavirus might play more significant roles (Shapiro RL, et al, 2001, Brooks JT et al, 2003) . Could this difference in etiology of diarrhea lead to differences in the effectiveness of zinc?

2. 2. Will zinc be as effective in an area with high HIV prevalence? HIV infection could influence the spectrum of pathogens or the immunologic response to zinc treatment.

3. Lastly, does treating acute diarrhea with zinc also prevent future episodes of diarrhea? This could have important programmatic implications as introducing zinc as a treatment for diarrhea is likely to be easier than introducing it as a preventive medication because people tend to be more compliant with medicines viewed curative rather than preventive.

Rationale for amendment – August 2006: The Kenya Ministry of Health (MOH) has recently decided that it will institute the use of zinc supplementation for 10-14 days, along with low osmolarity oral rehydration solution, for the management of diarrhoea in children under 5 years of age presenting in health facilities. This is the recommendation put forward in the joint statement for the clinical management of diarrhoea by WHO and UNICEF (Joint Statement on the Clinical Management of Diarrhoea. Geneva – New York, World Health Organization-UNICEF, 2004. Document (WHO/FCH/CAH04.7) The new management guidelines are planned to be implemented in last quarter 2006.

Because of these new treatment guidelines, the previous study design outlined in this protocol, whereby some children do not receive zinc for diarrhoea treatment, is no longer ethical. Therefore, we are changing the study design to answer important supplemental questions related to the new guidelines. In particular, we will evaluate whether access to home treatment with zinc and ORS can have an additional impact on diarrhea reduction in addition to their use in health facilities. The Kenyan MOH is interested in the results of this study to decide whether to roll out zinc treatment to the community level.

Update on Amendment March 26, 2007: The procurement of zinc has been delayed by the Kenya MOH because of lack of competitive bidders in the tender sent out for this in late 2006. Now it is likely zinc will not arrive in Kenya until late 2007. Until zinc arrives and becomes part of the essential drug kit, the study will provide zinc treatment in the clinic to children coming in with diarrhea. The indications and dosages will those recommended by WHO and the same as will be adopted by the Kenya MOH. Until zinc becomes part of the essential drug kit and available to all children in the clinic, only children who are enrolled in this study will receive zinc. When zinc does become part of the essential drug kit and available in the clinics, the children in the study will continue to receive zinc as before, and nonstudy children will also receive it.

Justification for the study. The use of zinc to treat or prevent diarrhea in Kenya has not been studied. The results of such a study among Kenyan children will be important in providing relevant information to the Ministry of Health to make policy decisions and in building within-country advocacy for scale-up of zinc use and whether to adopt a policy of community use of zinc, in addition to use in the health facilities, for diarrhea treatment. Because access to health care is poor in much of Kenya and most children with diarrhea do not go to health facilities, home-based treatment of diarrhea with zinc could be reach more children, and treat and prevent more diarrhea.

Statement of the null hypothesis. In villages in Western Kenya where children with acute diarrhea are treated (self-prescribed zinc/provided in home) with zinc and ORS at home in addition to the clinic, the prevalence of severe acute diarrhea will be the same as in villages where children with acute diarrhea are treated with zinc and ORS at the clinic only.

Objectives

*Primary*

1. To assess if access to zinc treatment for diarrhea in the home in addition to zinc treatment of diarrhea in the clinic leads to a greater reduction in the prevalence of diarrhea than giving zinc for treatment of diarrhea in the clinic only

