# Study design

*Study site and population* -- This study will take place the area of Asembo within 4.25 kilometers of Lwak Hospital where CDC’s IEIP program has ongoing population-based surveillance for infectious disease syndromes.

Since September 2001, KEMRI and CDC have collaborated to operate a demographic surveillance system (DSS) in Bondo and Siaya Districts in Western Kenya. Two rural study sites near Lake Victoria, Asembo and Gem, are covered by the DSS, totaling a population of approximately 130,000 people living in approximately 34,000 households. The area is large (almost 400 km2), culturally homogeneous (95% Luo tribe); subsistence farming and fishing constitute the principal economy. The area has perennial, high-level malaria transmission and a high rate of HIV infection (2003, >10% men, >20% women aged 13-34 years). Other infectious diseases are also common in the area. Consequently, the area has mortality figures that reflect this burden of infectious diseases --- infant mortality rate (120 per 1,000 live births) and a life expectancy at birth of 38 years. The area is one of the most impoverished in Kenya; 60-70% of people live below the poverty line in Siaya and >70% in Bondo (Kenyan Central Bureau of Statistics, 1997). The area has high rates of migration -- in 2002, the rate of out-migration was 115 per 1,000 person-years and in-migration was 124 per 1,000 person-years.

The Lwak surveillance area includes 33 villages, with an approximate enrolled population of 23,000 people. Enrollment of villages began in October 2005 and was completed in June 2006. Homes are visited every two weeks by field workers who enquire about symptoms of key infectious diseases, like diarrhea, respiratory infections and malaria. For key symptoms, like diarrhea, cough and fever, the actual number of days of symptoms are recorded. Some basic measurements, such as temperature and respiratory rate, are taken. Health seeking in the last two weeks is also asked about. This is being done for children and adults.

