## Sample size.

*Diarrhea Prevalence*.

The below calculations are for our primary study outcome of diarrhea prevalence.

Table 2a. Sample size estimates for various prevalences and reductions. Sample size table assumes a 5% reduction in diarrhea prevalence in the control group with a difference of 15% - 10% between groups.

| Difference in groups | Initial Prevalence in each group | N for each group initially/Total N | N for each group at end of trial/ Total N  (with 15% attrition) |
| --- | --- | --- | --- |
| 15% | 3.6 | 1059/2118 | 900/1800 |
| 14% |  | 1184/2368 | 1006/2012 |
| 13% |  | 1318/2636 | 1120/2240 |
| 12% |  | 1435/2870 | 1219/2438 |
| 11% |  | 1651/3302 | 1403/2806 |
| 10% |  | 3036/6072 | 2580/5160 |

Table 2b. Sample size estimates for various prevalences and reductions Sample size table assumes a 10% reduction in diarrhea prevalence in the control group with a difference of 15% - 10% between groups.

| Difference in groups | Initial Prevalence in each group | N for each group initially/Total N | N for each group at end of trial/ Total N  (with 15% attrition) |
| --- | --- | --- | --- |
| 15% | 3.6 | 1550/3100 | 1317/2634 |
| 14% |  | 1745/3490 | 1483/2966 |
| 13% |  | 1978/3956 | 1681/3362 |
| 12% |  | 2259/4518 | 1920/3840 |
| 11% |  | 2798/5596 | 2378/4756 |
| 10% |  | 4118/8236 | 3500/7000 |

We will assume 3.6 episodes per year of diarrhea in children in the study area, with an average duration of 3 days +/- 1 day. This gives a yearly prevalence of diarrhea of 10.8 days of diarrhea per child per year with a range of 7.2 to 14.4 days. We will also assume that because zinc use will increase gradually in the zinc villages as more children get diarrhea, it will take 6 months to achieve the indicated difference in diarrhea prevalence between the two groups (column 1). In the top table, it is assumed that there will be 5% reduction in diarrhea prevalence in the control group (nonhome zinc group) between the start of the study and end of the study 12 months later, due to the implementation of zinc in the clinic. The bottom table assumes that this reduction in the control group over the 12 months will be 10%.

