In this repeated measures, longitudinal study design, correlation between events must be accounted for. That is, some children will be more likely to have repeated diarrheal episodes and so will contribute disproportionately to the community prevalence. To do this, sample size calculations accounted for correlation by using the generalized estimating equation (GEE) method described by Rochon (Rochon J, 1998).

Approximately 14% of enrolled participants in the morbidity surveillance study are under 5 years of age. Therefore, we would expect in a population of 25,000 enrolled participants in the 33 villages in Lwak approximately 3,000 children under 5 years. Therefore, we will have the power to detect a difference of 12% between home zinc and nonhome zinc groups, assuming a 5% decrease in diarrhea prevalence in the nonhome zinc group during the study period, or a 15% difference between the home zinc and nonhome zinc groups, assuming a 10% decrease in diarrhea prevalence in the nonhome zinc group over the study period.

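### The same 33 villages are planned to yield about 1,300 children in the Abstract and about 3,000 in the Sample size section, and neither figure follows from the stated inputs

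*Protocol*

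**What the plan says.** The Abstract (Work planned) gives the size of the trial: "Thirty-three villages (approximately 1300 children) will be enrolled and children will be followed for 1 year".

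The Sample size section gives a different size for the same villages. It starts from an age share, "Approximately 14% of enrolled participants in the morbidity surveillance study are under 5 years of age", and concludes that "we would expect in a population of 25,000 enrolled participants in the 33 villages in Lwak approximately 3,000 children under 5 years". From that number it claims that "we will have the power to detect a difference of 12% between home zinc and nonhome zinc groups" if prevalence in the comparison group falls by 5%, "or a 15% difference between the home zinc and nonhome zinc groups, assuming a 10% decrease in diarrhea prevalence in the nonhome zinc group".

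The tables behind these claims list numbers at the start and, after 15% attrition, at the end of the trial. The 15% row of Table 2b reads "1550/3100 | 1317/2634" (per group/total at the start, then the same at the end).

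The Study design section gives a smaller base population than the 25,000 used for power: "The Lwak surveillance area includes 33 villages, with an approximate enrolled population of 23,000 people".

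Under Randomization, the text assigns 16 or 17 villages to each arm. The flow chart there opens with 33 villages and then shows 15 in each arm.

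**The concern.** The number of children and the detectable difference are what a funder or ethics committee uses to judge whether the trial can answer its question. Here the number of villages is the same in both places and the number of children is not. The gap is far beyond rounding. If the Abstract figure were the true expectation, the power statement would have no support in the protocol's own tables. If the power section figure is meant, the Abstract misstates the trial, and the figure still does not match the share and population given beside it. The flow chart matters less, but the village is the randomized unit, so its count per arm should be right.

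**Working it through.** **Inputs, all from the Protocol.** Children: 1,300 (Abstract); 3,000 (Sample size). Share under 5: 14% (Sample size). Population: 25,000 (Sample size); 23,000 (Study design). Initial totals: 2,870 for a 12% difference and 2,118 for 15% (Table 2a); 3,100 for 15% (Table 2b). Attrition: 15%. Significance level: 0.05 (Data Analysis).

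**1. The two planned numbers.** 3,000 / 1,300 = 2.3. Per village, 1,300 / 33 = 39 and 3,000 / 33 = 91.

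**2. Reproducing the 3,000.** Expected number = share × population.
- 0.14 × 25,000 = 3,500
- 0.14 × 23,000 = 3,220

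Neither gives 3,000, which would need 3,000 / 25,000 = 12% of the larger population. The Abstract figure is further off: 1,300 / 23,000 = 5.7%.

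**3. Reproducing the tables.** End number = initial number × 0.85. For example, 1,059 × 0.85 = 900.2 (stated 900) and 1,550 × 0.85 = 1,317.5 (stated 1,317). All 12 rows agree. The initial numbers themselves cannot be checked, because the section states neither the power nor the correlation used in the GEE method. They are taken as given below.

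**4. Which column the claims use.** With 3,000 children, the initial column of Table 2a allows 12% (2,870) but not 11% (3,302), which matches the claim. The end-of-trial column would have allowed 11% in Table 2a (2,806) and 14% in Table 2b (2,966). The claims were therefore read from the initial column.

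**5. Testing each number against the tables.**

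| Children at start | Table 2a, 12% (needs 2,870) | Table 2b, 15% (needs 3,100) |
| --- | --- | --- |
| 1,300 | not met | not met |
| 3,000 | met | short by 100 (3.2%) |
| 3,220 | met | met |
| 3,500 | met | met |

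After attrition, 3,000 × 0.85 = 2,550 against 2,634 in Table 2b. At 1,300 the shortfall covers all 12 rows: 1,300 / 2,118 = 61% of the smallest requirement, and 1,300 × 0.85 = 1,105 against 1,800 at the end.

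**6. What this means in power.** Hold the difference fixed and let the variance fall as 1/N. Then power = Φ[(1.960 + z) × √(N / N_table) − 1.960], where z is 0.842 for 80% and 1.282 for 90%. A two-sided test and these two power levels are assumptions; the protocol states neither.

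| Case | If tables assume 80% | If tables assume 90% |
| --- | --- | --- |
| 3,000, Table 2b 15% | 79% | 89% |
| 1,300, Table 2a 12% | 47% | 59% |
| 1,300, Table 2b 15% | 44% | 56% |

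For the first entry: √(3,000 / 3,100) = 0.984; 2.802 × 0.984 − 1.960 = 0.796; Φ(0.796) = 0.787.

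**7. Villages.** Flow chart arms: 15 + 15 = 30, against 33 in its own first box and 16 + 17 = 33 in the text. The serum zinc sample agrees with 33: 165 children at 5 per village is 165 / 5 = 33.

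**The case against.** The best defence is that 1,300 is an isolated slip. It appears once, while the power section works with 3,000 and the stated share and population point to 3,000 or more. On that reading the trial is adequately sized by its own tables, and only the Abstract needs correcting. Much of this stands: the documents favour the larger number, and the power statement fails badly only if 1,300 governs. But nothing in the protocol says that 1,300 is superseded or what else it might count. It cannot be one arm, since 33 villages is both arms, and even doubled it is 2,600, below 2,870 and 3,100.

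It is also fair to say that 3,000 against 3,100 is a small gap between approximate figures. That is accepted, and it closes once the stated 14% is applied.

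A reader might go on to infer three stronger things that the documents do not support.

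- *That the 12% row of Table 2a is faulty.* Scaling by the inverse square of the difference from the adjacent rows gives 2,636 × (13/12)² = 3,094 and 3,302 × (11/12)² = 2,775. The stated 2,870 lies between them.
- *That 1,300 children could detect about 18–19% (Table 2a) or 23% (Table 2b).* This uses the same inverse-square rule, under which the total number times the squared difference should be constant. It is not: it runs from 399,542 (11% row) to 607,200 (10% row) in Table 2a, and from 650,592 (12% row) to 823,600 (10% row) in Table 2b. The tables show only that 1,300 is below every row.
- *That 3,000 assumes every child under 5 is eligible and consents.* It is already below the full count implied by the inputs, by 220 / 3,220 = 7% to 500 / 3,500 = 14%. The protocol does not explain the difference, so one cannot say that it makes no allowance.

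**Conclusion.** The planned number of children is wrong as written and should be corrected. The two stated figures differ 2.3-fold for the same 33 villages, and neither follows from the share and population figures given. The consequence depends on which number is real:

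- at 1,300, neither claimed difference is supported, and nor is any other row of the tables;
- at 3,000, the 12% claim holds and the 15% claim is marginally short;
- at 3,220 to 3,500, both hold.

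This takes the initial numbers in Tables 2a and 2b as correct, which could not be verified. The power percentages also rest on an assumed two-sided test and an assumed 80% or 90% power; the comparison with the table rows does not. The shortfall against 3,100 and the 30 villages in the flow chart are true but minor. It would go too far to conclude that the trial is underpowered: the protocol's own inputs point to enough children, and what is missing is one consistent figure.

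**What to change.** 1. Derive one expected number of eligible, consenting children aged 2–59 months, either from the surveillance register of the 33 villages or from one population figure and one under-5 share, with any allowance for eligibility and consent stated.
2. Use that number in both the Abstract and the Sample size section, and reconcile the 23,000 and 25,000.
3. Restate the detectable difference for that number from the initial column of Tables 2a and 2b. For example, 3,220 supports 12% and 15%, while 3,500 would reach 11% (3,302) and 14% (3,490).
4. Change the flow chart arms to 16 and 17 villages.

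The cost is a register count, a table look-up and text edits. The design and procedures do not change. If the count comes out near 1,300, the power statement has to be withdrawn and recalculated, because the existing tables do not extend that far.
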